## Abstract

Latinos bear a disproportionate burden of the dual pandemic of obesity and diabetes. However, successful interventions addressing this disparity through primary care are lacking. To address this gap, the 5-year Vida Sana (Healthy Life) study tests a culturally adapted and technology-enhanced group-based Diabetes Prevention Program intervention in a randomized controlled trial with overweight/obese Latino adults who have metabolic syndrome and/or pre-diabetes. Eligible, consenting patients (n=186) from a large community-based multispecialty group practice in Northern California will be randomly assigned to receive the culturally-adapted intervention or usual care. The RE-AIM (Reach, Effectiveness, Adoption, Implementation, and Maintenance) framework guided the planned evaluations. The primary aim is to determine the effectiveness of the intervention (the “E” in RE-AIM). We hypothesize that the intervention will lead to a greater mean reduction in weight at 24 months (primary endpoint) vs. usual care. Secondary outcomes will include measures of cardiometabolic risk factors (e.g., blood pressure), psychosocial well-being (e.g., health-related quality of life), and behavior change (e.g., physical activity). The secondary aim is to evaluate the other RE-AIM dimensions using mixed methods: reach (e.g., participation rate of the target population), adoption (e.g., participating clinic and provider characteristics), implementation (e.g., intervention fidelity), and maintenance (e.g., sustainability in the practice setting). These findings have real world applicability with value to clinicians, patients, and other decision makers considering effective diabetes prevention programs for primary care that would support the millions of Latino adults who experience a disproportionate burden of diabetes.

Word count: 240

Trial registration: NCT02459691

## 1. Introduction

Ranking as the largest and fastest growing minority group in the United States (US), Latinos reached 55 million in 2014. The prevalence of overweight and obesity is higher among Latino adults (77%) than non-Hispanic whites (68%). Consequently, Latinos have a higher incidence of type 2 diabetes and prevalence of major cardiovascular risk factors (e.g., metabolic syndrome, pre-diabetes).

Previous studies have shown that behavioral lifestyle interventions are effective for promoting modest yet clinically significant weight loss and can delay or prevent the onset of diabetes in high-risk adults in community and primary care settings. For example, the Diabetes Prevention Program (DPP) trial showed an intensive lifestyle intervention targeting modest weight loss (7%) and increased physical activity (150 minutes per week) lowered type 2 diabetes incidence by 58% among high-risk, multiethnic adults (55% non-Hispanic whites, 20% black, and 16% Hispanic/Latino). Follow-up data showed that the intervention benefits persisted for at least 10 years. To promote dissemination, the original, resource intensive, primarily one-on-one curriculum was adapted to a group program with fewer sessions, called Group Lifestyle Balance (GLB). The one-year GLB curriculum is approved by the Centers for Disease Control and Prevention through the national Diabetes Prevention Recognition Program^17 and has been proven to be feasible and effective in community and primary care settings.

Technology has potential to increase the reach, effectiveness, and scalability of behavioral lifestyle interventions such as the GLB. We previously demonstrated the effectiveness of supplementing the GLB 12-session core curriculum with technology-mediated lifestyle coaching via secure email messaging and web-based self-monitoring of weight and physical activity to reduce obesity and cardiometabolic risk factors in a primary care setting in the E-LITE (Evaluation of lifestyle interventions to treat elevated cardiometabolic risk in primary care) study. However, similar to other rigorous lifestyle intervention trials in primary care, Latinos were <5% of total participants. Communication technologies (e.g., web, email, mobile) and wearable devices (e.g., pedometers, accelerometers) offer opportunities to tailor interventions to diverse subgroups such as Latinos as well as to promote effectiveness by adapting to individuals' response to interventions over time.

The primary care setting is ideal given opportunities for primary care physicians to refer at-risk patients, provide on-going management for comorbidities, and support maintenance of preventive lifestyle behaviors. For Latinos, increasing access to healthcare as a result of the Affordable Care Act (for those eligible for insurance or with insurance), makes primary care-based programs increasingly advantageous. Additionally, behavioral lifestyle interventions based in primary care provide an opportunity to provide healthcare for Latinos that is personal, welcoming and concerned for the individual in a social context, which is favored by Latino cultural values.

To date, few effective and practical behavioral weight-loss interventions that leverage technology and are based in primary care have been developed and tested among high-risk Latinos: a large, vulnerable population with persistent health disparities. To fill this critical gap, the Vida Sana (Healthy Life) study was designed to evaluate a culturally-adapted, technology-enhanced intervention targeting overweight or obese Latino adults with pre-diabetes, a history of gestational diabetes, and/or metabolic syndrome in a community primary care setting.

## 2. Methods

### 2.1. Study Design

This pragmatic RCT (11/2014-08/2019) will evaluate a culturally-adapted intervention based on the Group Lifestyle Intervention among high-risk Latino adults. For the purposes of this study, 'Latino' refers to people who self-identify as Latino or Hispanic. The culturally adapted intervention was developed through rigorous formative research and pretesting by a Latino Patient Advisory Board. The specific aims focus on the primary outcome of weight and the evaluation of the domains of the RE-AIM (Reach, Effectiveness, Adoption, Implementation, and Maintenance) framework.

**Aim 1:** Compare the culturally-adapted intervention and usual care for overweight or obese Latino adults with pre-diabetes and/or metabolic syndrome, but without diabetes or cardiovascular disease (the E in RE-AIM).

**Hypothesis 1:** Compared with controls, intervention participants will achieve a greater mean reduction in weight from baseline to 24 months (primary outcome).

**Hypothesis 2:** Compared with controls, intervention participants will achieve greater improvements in secondary outcomes including measures of cardiometabolic risk factors (e.g., Body Mass Index, waist circumference, and blood pressure), psychosocial well-being (e.g., health-related quality of life), and lifestyle behaviors (e.g., diet, physical activity).

**Aim 2:** Assess intervention attributes in the other RE-AIM domains to gauge generalizability and guide future implementation.

We will use mixed methods to measure other four RE-AIM attributes: Reach, Adoption, Implementation, and Maintenance; and conduct subgroup and effect mediation analyses to explore which patients benefit more and how so.

### 2.2. Pragmatic RCT

#### 2.2.1. Eligibility Criteria

We will apply permissive inclusion criteria and minimally necessary exclusion criteria to optimize the balance between generalizability, patient safety, intervention adherence, and retention. We will enroll Spanish-speaking or bilingual Latino adults  $\geq 18$  years with a BMI  $\geq 24$  kg/m^2 ( $\geq 22$  if of Asian ancestry) and pre-diabetes, a history of gestational diabetes, and/or metabolic syndrome, but without type 1 or type 2 diabetes or cardiovascular disease (**Table 1**) who are active patients at the Palo Alto Medical Foundation (PAMF), a large community-based multispecialty group practice in Northern California. Patients with significant psychiatric (e.g., bipolar or psychotic disorder) or medical comorbidities (e.g., active cancer, organ failure) will be excluded. Additional exclusions are to protect participant safety (e.g., pregnancy) and prevent loss to follow-up (e.g., planned relocation, limited lifespan).

#### 2.2.2. Recruitment and Screening

The targeted enrollment of 186 participants will be met in three sequential cohorts of 62 patients each. Each cohort will be recruited from one of three different clinic sites within PAMF where participants randomly assigned to the intervention group will attend the group sessions. Recruitment and screening will proceed in four steps. First, PAMF patient EHRs will be pre-

screened to identify potential participants meeting basic eligibility criteria (e.g., age, active patient status, and absence of exclusionary medical or psychiatric comorbidities). Second, Primary Care Physicians (PCPs) at each site will review lists of potentially eligible patients, exclude those they deem inappropriate for the study because of medical reasons, and authorize study contact for the rest. Third, PCP-approved patients will receive a recruitment email or letter in Spanish and English introducing the study and inviting them to complete an initial brief screening online, which focuses on those eligibility criteria that individuals can reliably assess themselves (e.g., pregnancy, likelihood of relocation). Two weeks after sending the email or letter, recruitment staff will phone patients who have not done self-screening and who did not opt out, to complete the initial screening. Fourth, patients who screen eligible will complete an in-person baseline visit at the clinic site from which they were recruited. Prior to the visit, patients will receive the link to a self-administered survey for completion prior to the in-person visit so as to reduce the overall time of the visit. If patients cannot or do not want to complete the survey prior to the visit, they can do so at the visit. The visit will begin with obtaining written informed consent. A trained bilingual research assistant will orally administer the baseline questionnaire and conduct standardized height, weight, waist circumference, and blood pressure measurements.

### 2.2.3. Randomization and Blinding

Eligible participants will be randomized in a 1:1 ratio to receive usual care or usual care plus the intervention ( $n = 93/\text{arm}$ ). We will apply a covariate-adaptive biased coin method that we have published and used successfully in several trials to achieve good marginal balance between treatments across the following baseline characteristics: clinic, age, sex, BMI, waist circumference, and level of acculturation assessed by the Short Acculturation Scale for Hispanics. The dynamic block randomization algorithm of our method automatically ensures allocation concealment. By design, treatment will be identifiable to participants and the lifestyle coach, but masking of the investigators, Data and Safety Monitoring Board, outcome assessors, and data analyst will be enforced. The bilingual and bicultural lifestyle coach will be masked to participants' official study measurements, but not their self-measurements tracked on MyFitnessPal.

### 2.2.4. Continuation of Usual Care

For patient safety and generalizability, no standard care will be withheld at any time after enrollment. We will recruit from patients who have used PAMF for routine care for  $\geq$  one year and thus have a higher likelihood of establishing a relationship with their PCP. Regardless of treatment assignment, participants will not be restricted from seeking weight loss treatment from their physician or in the community, to control for changes in medical practice and secular trends and to protect external validity. From the EHR we will determine PCP orders and referrals throughout the trial period for intervention and control participants. We will also survey participants about any programs or products that they may have used on their own to treat obesity during the trial. We will conduct secondary analyses using data on out-of-study obesity treatments to elucidate their potential confounding effects on the primary intention-to-treat (ITT) findings. Based on EHR and survey data collected in E-LITE, 15 of the 81 controls used an out-of-study weight loss program (13 used a commercial and two used a PAMF program), compared with five of the 79 coach-led and three of the 81 self-directed participants (all used a commercial program), during the 15-month trial period ( $P = .003$ ). No one underwent pharmacological or surgical weight loss treatment. These data suggest a low participation rate

in non-study programs among research participants; to the extent that it occurred in E-LITE, it supported the robustness of the primary ITT findings.

## 2.2.5. Intervention and Fidelity Assurance

In addition to usual care, intervention participants will receive a culturally-adapted intervention facilitated by a trained bilingual/bicultural coach. The intervention sessions will take place at the clinic site where the patient was recruited.

### 2.2.5.1. Theoretical basis

The intervention is based on Social Cognitive Theory, which emphasizes a triadic, reciprocally deterministic relationship between the individual, environment, and behavior. It recognizes that behavior change is a dynamic process that moves at variable speed through stages of readiness to change. Positive outcome expectancies through realistic goal setting and guided action planning are associated with initiation of behavior change. Self-efficacy developed for specific behaviors (e.g., physical activity) predict establishment and maintenance of behavior change. Social Cognitive Theory suggests that self-efficacy is enhanced through social support and gradual mastery of self-regulation skills (e.g., goal setting, self-monitoring).

### 2.2.5.2. Vida Sana format and lifestyle coach

The Vida Sana intervention is a cultural adaptation of the original GLB. The program is delivered in Spanish with Spanish-language handouts and utilizes Smartphone and web applications that are available in Spanish. A bilingual and bicultural lifestyle coach with a bachelor's degree who undergoes standard training with a GLB master trainer (see 2.2.5.5) delivers the intervention. Information about the 2-day GLB standard coach training can be found on the website of the University of Pittsburgh Diabetes Prevention Support Center. The lifestyle coach does not need additional training or advanced degrees to serve in this role.

As in the original GLB curriculum, the Vida Sana intervention has two distinct components: 1) intensive treatment (core) and 2) post-core support. The intensive treatment component includes 12 weekly core sessions followed by four bi-weekly core transition sessions, for a total of 16 sessions delivered within the first six months of the program. It uses a goal-based approach to promote positive outcome expectancies and foster self-efficacy by targeting at least 7% weight loss and a minimum of 150 minutes per week of moderate-intensity physical activity. Moderate caloric reduction by 500-1,000 kcal/day through healthy substitutions and portion control, rather than omission or elimination of specific foods, is recommended. The post core support phase includes an additional six sessions delivered monthly over the course of six months for a total intervention duration of 12 months. Post core support phase focuses on (1) facilitating continued behavior change through an iterative guided mastery process; (2) fostering participants' self-efficacy and independence; and (3) reinforcing problem-solving and behavior maintenance skills. A healthy meal, often a healthy version of a traditional dish, is provided at each session.

Formative research and pretesting by a Latino Patient Advisory Board informed the cultural adaptations for Vida Sana. The Vida Sana intervention builds upon references to family in the original GLB and includes three opportunities to include family members during the in-person group sessions. First, Vida Sana includes a family-wide orientation session prior to Session 1. This provides an opportunity for the lifestyle coach to describe the Vida Sana intervention to the family and to provide family members with concrete strategies for demonstrating emotional,

structural, and informational support to the participant. In addition, families are encouraged to engage in fun activities to promote a positive family environment that is supportive for lifestyle changes. Second, the lifestyle coach encourages participants to invite one family member to Session 6: “Take Charge of What is Around You.” This session focuses on modifying the physical and social environment to promote healthy behaviors. Family members are engaged to work with the participant to identify and make these changes. Third, participants are encouraged to bring a family member to session 12 after which the frequency of the sessions reduces to bimonthly and monthly. At session 12, family members are encouraged to provide support during this transition. In addition to the emphasis on family, the Vida Sana intervention includes other modifications that were recommended by the Latino Patient Advisory Board. For example, the MyPlate graphic and recommendations is introduced in session 1 as opposed to session 3 in the original GLB. Similarly, the physical activity monitor is introduced in session 1 as opposed to session 4 in the original GLB. These additions to session 1 were made possible by the addition of the family-wide orientation session that covered information on the program that was originally covered in GLB session 1. Other modifications were primarily superficial changes to example foods or example situations.

#### 2.2.5.3. Technology-enhanced coaching and self-monitoring

Based on the success of the E-LITE trial, the culturally-adapted intervention incorporates self-monitoring via MyFitnessPal on a mobile device or computer, a wireless physical activity monitor (FitBit), and individualized feedback through the Smartphone application. Self-monitoring is key to success in behavioral weight-loss interventions. Participants are encouraged to track their weight, diet and physical activity on a daily basis through the MyFitnessPal application, which is available in Spanish. Pedometer-measured daily steps are captured via the FitBit activity monitor and automatically synched with the FitBit Smartphone or web application. The coach reviews participants’ self-monitoring data and provides individualized feedback via the Smartphone application every week during the core phase and in response to participants’ needs in the post-core phase. The coach provides feedback and counseling on actionable lifestyle change and problem-solving strategies (e.g., to reduce intake of fat and calories) to help participants reach their goal of 7% weight loss and 150 minutes of physical activity. Additionally, for 12 months following the intervention, the coach sends monthly messages to all participants reinforcing intervention topics and offering support for maintenance of lifestyle behaviors. This form of coach-participant interaction is intended to support the participant in tailoring the implementation of recommended lifestyle change strategies to achieve feasibility and sustainability within their own home and social environments, and to aid in problem solving and relapse prevention. The coach focuses on dietary change, physical activity, and behavioral skills training suited to what each participant is eating and doing, and the changes (s)he is willing and able to make given his or her own resources and supports. These added features will likely enhance the proposed intervention’s reach and adoption potential given the prevalence of online and mobile technology use among US Latinos.

#### 2.2.5.4. Fidelity assurance

We will follow recommendations for quality assurance in behavioral interventions. Use of standardized intervention materials, structured staff training and ongoing oversight are fundamental to ensuring high intervention fidelity. The lifestyle coach will undergo standardized training by a certified GLB master trainer with supplemental training on the cultural adaptations resulting from the formative research. Per our standard practice, all group sessions will be audiotaped and a random 10% sample from the sessions by recruitment cohort will be audited and graded using a session-by-session rating scale from a previous trial. The coach will complete a checklist of critical intervention behaviors and materials delivered during each

session. Self-monitoring records and Smartphone application communication are readily retrievable and will be reviewed as part of routine quality control efforts. Falling below an a priori performance standard (e.g., 90% adherence to intervention protocol) will trigger more frequent audit and feedback and, if needed, “booster” training for the coach. Participant engagement and adherence are also essential to intervention fidelity and must be monitored and supported. Participant progress on key intervention tracking parameters (e.g., date, format, duration of contact, most current weight, and physical activity level) will be routinely documented. The coach will review and give feedback on homework and self-monitoring records and document participant progress toward protocol-specific, achievement-based objectives. She will routinely inquire about barriers to intervention receipt and adherence, recommend personalized, actionable problem-solving strategies, and provide ongoing support via proactive follow-up.

#### 2.2.6. Participant Safety

PCP approval will be required before potentially eligible patients are contacted by the study. Participants will be carefully screened and individuals for whom the interventions would be medically inappropriate or unsafe are excluded. During screening, women who are pregnant, lactating, or planning to become pregnant during the study period are excluded. If a participant becomes pregnant during the study, she is excluded immediately from further participation in all study activities, and her PCP is immediately notified. Participants who develop any other exclusionary condition (e.g., diabetes) following randomization may continue with the interventions and follow-up assessments with their PCP’s approval. To ensure unbiased ascertainment between the intervention and control group, outcome assessors will systematically screen all participants for adverse events during in-person assessments at baseline, 12, and 24 months using a standard interview and reporting form as done in our previous trials. In addition, outcome assessors will call all patients at six and 18 months to screen for adverse events. Positive responses trigger an adverse event record, which is reviewed by the study physician for seriousness, study relatedness, and expectedness. Similar information reported by participants at other times (e.g., during intervention encounters) is duly noted and followed up with, as needed, to assure participant safety. Participants will be referred to their PCP for a medical evaluation and follow-up as needed or recommended by the study physician. We will report adverse events according to the data and safety monitoring plan (**Appendix A**).

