### 2.2.8.1. Primary and secondary outcomes (Aim 1)

Primary outcome, weight, will be assessed according to standard protocols. Secondary outcomes include measures of cardiometabolic risk factors (e.g., BMI, waist circumference, and blood pressure), psychosocial well-being (e.g., health-related quality of life), and behavior change (e.g., diet, physical activity). Trained bilingual research assistants will conduct anthropometric and blood pressure measurements, and multiple-pass 24-hour dietary recalls. Online self-administered questionnaires and in-person interviewer-administered questionnaires (see **Table 2**) will be used to assess additional secondary outcomes including physical activity, health-related quality of life, obesity-specific quality of life, depressive symptoms, and sleep habits and quality. All these surveys have been validated in English and Spanish. Additionally, we will abstract data from the EHR on laboratory values (e.g., HbA1c, fasting glucose, lipid levels), medication prescriptions, and health care encounters for 24 months before and after randomization.

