## 2.2.9. Statistical Analysis

### 2.2.9.1. Analytical plan

The primary hypothesis that intervention participants will achieve and maintain lower weight at 24 months than controls will be tested in a repeated-measures mixed model (Aim 1). Secondary hypotheses are analogous, but with different outcome variables, and will be tested using repeated-measures, mixed-effects, linear (for continuous variables) or logistic models (for discrete variables).

$$Y_t = \beta_0 + \beta_1 X + \beta_2 Y_0 + \beta_3 T + \beta_4 (XT) + \sum \beta_{4+i} Z_i + \alpha + \gamma + \varepsilon \quad (1)$$

Let  $Y_t$  be participants' post-randomization values of the outcome variable at visit T (12 or 24 months). Given the covariate-adaptive randomization, distributions of baseline values on the outcome variable ( $Y_0$ ) and randomization balancing factors ( $Z_i$ ) (clinic, age, sex, BMI, waist circumference, and level of acculturation) should be similar between study arms (X) and thus not bias the results. But to the extent they are associated with the outcome, their inclusion in the model will account for otherwise unexplained variation and hence increase efficiency;  $\alpha$  and  $\gamma$  are random effects due to clustering of patients within physicians and, in turn, physician within clinics, and patients with intervention classes. The random error,  $\varepsilon$ , accounts for the non-independence of repeated measures using a covariance structure within participants to be determined by the least Bayesian information criterion. The primary analysis will follow ITT principles and use all available follow-up data, with missing data handled directly through maximum likelihood estimation in mixed modeling. We will document the extent and pattern of missing data and the reasons, and will conduct sensitivity analyses of the impact of missing data on stability of the primary results. For example, we may use available weights up to the point after which data are no longer available (e.g., dropouts) or should not be used (e.g., pregnancy) and then employ multiple imputation based on a predictive distribution for future weights with the mean possibly adjusted depending on the pattern and extent of missing data. We will verify that mixed model-based results are not sensitive to violations of model assumptions with permutation and bootstrap resampling tests.

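### The safety section does not separate stopping the intervention from stopping outcome weighing, so 12- and 24-month weights can be lost after pregnancy or incident diabetes

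*Protocol*

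**What the plan says.** Section 2.2.6 (Participant Safety) has two rules for events after randomisation.

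- Pregnancy: "If a participant becomes pregnant during the study, she is excluded immediately from further participation in all study activities".
- Any other exclusionary condition, with diabetes as the example: such participants "following randomization may continue with the interventions and follow-up assessments with their" PCP's approval.

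The same section has outcome assessors screen all participants for adverse events at the 12- and 24-month visits, and call everyone at 6 and 18 months, so that ascertainment is unbiased between arms. Section 2.2.7 plans to re-engage people who miss visits.

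Section 2.2.9.1 states: "The primary analysis will follow ITT principles and use all available follow-up data, with missing data handled directly through maximum likelihood" estimation. It commits to recording the extent, pattern and reasons of missing data and to sensitivity analyses. As one possible approach it would truncate weights at the point where "data are no longer available (e.g., dropouts) or should not be used (e.g., pregnancy) and then employ multiple imputation". In equation 1 the outcomes are the 12- and 24-month values only, and baseline weight is a covariate.

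Section 2.2.3 lists as masked the investigators, the DSMB, the outcome assessors and the data analyst. PCPs are not on that list. Section 2.2.8.1 abstracts from the EHR laboratory values, "medication prescriptions, and health care encounters for 24 months before and after randomization". Clinic weights are not named.

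**The concern.** Whether a participant goes on with a treatment and whether that participant is weighed at 24 months are different questions. Section 2.2.6 answers them with one rule. In the usual-care arm there is no study intervention to continue, so there the PCP's approval decides only whether the outcome is measured.

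The trigger is not neutral. The trial enrols people with pre-diabetes, metabolic syndrome or both. The Introduction cites a 58% reduction in diabetes incidence from the lifestyle programme on which this one is modelled. Incident diabetes is thus expected to differ by arm on the protocol's own rationale, and it is plausibly related to weight change. If weights are lost after it, the loss may depend on outcome and arm, whereas maximum likelihood relies on data being missing at random given what was observed. A participant stopped before month 12 has no follow-up weight at all and supplies no outcome row to equation 1.

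At stake are some bias in the primary 24-month difference and some loss of precision. An analysis plan written later cannot recover a weight that was never taken.

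**Working it through.** **1. The texts side by side.** Someone removed from all study activities under section 2.2.6 cannot be screened or telephoned as the same section requires for all participants. That needs reconciling. Section 2.2.9.1 promises ITT on available data, not complete follow-up, so it is weakened but not contradicted. It foresees pregnancy. It does not mention weights lost because a PCP withholds approval.

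**2. The plan's own sample size.** Inputs from section 2.2.9.2: difference 2.1 kg, SD 4.6 kg, two-sided 5%, 80% power, up to 20% loss, 93 per arm.

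- n per arm = 2 × (1.960 + 0.842)² × 4.6² / 2.1² = 75.3, so 76 evaluable (76.3 by t-test).
- 76 / 0.8 = 95; 76 × 1.2 = 91.2, so 92. The stated 93 lies between.
- 93 × 0.8 = 74.4 evaluable gives 79.5% power (normal approximation; 79.0% by t-test).

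The stated figure reproduces and is not in dispute.

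**3. Bias if every converter is lost.** Assumptions not in the protocol: control conversion p of 5 or 10% over 24 months, and weight change in converters D = 2 to 6 kg above the rest of their arm. From the Introduction: intervention conversion = (1 − 0.58) × p = 0.42p, that is 2.1 or 4.2%.

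Losing a fraction f of an arm lowers that arm's observed mean change by f × D. The shift in the between-arm difference is (p − 0.42p) × D = 0.58 × p × D.

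| p | D | Shift (kg) | Share of 2.1 kg |
|---|---|---|---|
| 5% | 2 kg | 0.058 | 3% |
| 5% | 6 kg | 0.174 | 8% |
| 10% | 2 kg | 0.116 | 6% |
| 10% | 6 kg | 0.348 | 17% |

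With D positive, controls look lighter than they are and the difference moves toward zero. With equal loss and equal D in both arms the shift is zero.

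**4. Partial refusal.** If only a share r of converters is lost, an arm's shift is p × D × r × (1 − p) / (1 − r × p). Taking the control value minus the intervention value:

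- r = 50% (assumed): about 0.03 to 0.16 kg.
- r = 20% (assumed): about 0.01 to 0.06 kg.

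**5. Power.** With 74.4 evaluable per arm, the standard error is 4.6 × √(2/74.4) = 0.754 kg. Shifts of 0.06, 0.17 and 0.35 kg bring power from 79.5% to about 77%, 72% and 64%. Separately, if such losses came on top of the 20% allowance, an extra 2, 5 or 10% loss would give 78.5%, 76.9% or 74.0%. The allowance may already cover them.

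**The case against.** A reader might infer that section 2.2.6 contradicts the ITT analysis. It does not: section 2.2.9.1 uses all available data, weights already collected stay in, and a missing-data sensitivity analysis is a commitment. The example given there lets the imputed mean be adjusted to the pattern of missingness, which allows for data not missing at random. That method is only something the team may use, but its detail may properly sit in an analysis plan.

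A reader might also infer that participants with incident diabetes are removed. The text lets them continue, so a weight is lost only where a PCP refuses. Nothing in the protocol suggests that refusal would be common, and these PCPs approved study contact in the first place. Table 2 schedules no study blood test at follow-up, since glucose and HbA1c come from the EHR. A case first noted at the 24-month visit need not cost the 24-month weight.

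Pregnancy is anticipated in the analysis section, and women planning pregnancy are excluded at screening, so cases should be few. No arm imbalance is evident for it.

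Much larger biases can be produced. Conversion of 30% with a 5 kg difference gives 0.58 × 0.30 × 5 = 0.87 kg, 41% of the target. That needs a conversion rate found nowhere in the protocol together with universal refusal. The direction is assumed too: if PCPs refused more often for intervention participants, the shift could shrink or reverse.

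All of this stands as a limit on size. None of it answers the structural point that weighing is tied to permission to continue.

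**Conclusion.** The point holds at moderate severity. As written, section 2.2.6 can cost 12- and 24-month weights after pregnancy, and after incident diabetes where approval is withheld by a PCP who is not listed as masked. This weakens the ITT analysis and sits badly with the section's own plan to screen everyone.

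The 0.06 to 0.35 kg range is an illustration. It rests on assumed conversion and weight differences, on carrying over the cited 58% reduction, and on loss of every converter. It also describes a completer contrast: the planned mixed model recovers part of the shift when a 12-month weight exists. The pregnancy rule is not quantified. The documents do not support calling the primary analysis invalid, or the shift a likely source of a false positive result.

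**What to change.** Reconcile sections 2.2.6 and 2.2.9.1 by a short amendment.

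- State collection of the 12- and 24-month outcome weights separately from continuing the intervention, and retain it for every randomised participant who still consents. Leave the clinical rules on the intervention and on pregnancy unchanged; how they fit with the separate weighing statement is for the sponsor to settle.
- State that weights affected by pregnancy are handled as section 2.2.9.1 describes, and that a 24-month weight no longer affected by pregnancy may be collected if the reconciled safety rule allows it.
- Say how weights missing because approval was withheld enter the sensitivity analysis already promised.
- Add clinic-recorded weights to the EHR abstraction in section 2.2.8.1, as auxiliary data for that sensitivity analysis only.

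The cost is the amendment and one more EHR field. EHR weights are not taken to the study's standard, so they should not replace the study measurement.
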